## Abstract

**Background:**

Healthy lifestyle interventions have a positive impact on multiple disease trajectories, including cancer-related outcomes. Specifically, appropriate habitual physical activity, adequate sleep, and a regular wholesome diet are of paramount importance for the wellness and supportive care of survivors of cancer. Mobile health (mHealth) apps have the potential to support novel tailored lifestyle interventions.

**Objective:**

This observational pilot study aims to assess the feasibility of mHealth multidimensional longitudinal monitoring in survivors of cancer. The primary objective is to test the compliance (user engagement) with the monitoring solution. Secondary objectives include recording clinically relevant subjective and objective measures collected through the digital solution.

**Methods:**

This is a monocentric pilot study taking place in Bangor, Wales, United Kingdom. We plan to enroll up to 100 adult survivors of cancer not receiving toxic anticancer treatment, who will provide self-reported behavioral data recorded via a dedicated app and validated questionnaires and objective data automatically collected by a paired smartwatch over 16 weeks. The participants will continue with their normal routine surveillance care for their cancer. The primary end point is feasibility (eg, mHealth monitoring acceptability). Composite secondary end points include clinically relevant patient-reported outcome measures (eg, the Edmonton Symptom Assessment System score) and objective physiological measures (eg, step counts). This trial received a favorable ethical review in May 2023 (Integrated Research Application System 301068).

**Results:**

This study is part of an array of pilots within a European Union funded project, entitled “GATEKEEPER,” conducted at different sites across Europe and covering various chronic diseases. Study accrual is anticipated to commence in January 2024 and continue until June 2024. It is hypothesized that mHealth monitoring will be feasible in survivors of cancer; specifically, at least 50% (50/100) of the participants will engage with the app at least once a week in 8 of the 16 study weeks.

**Conclusions:**

In a population with potentially complex clinical needs, this pilot study will test the feasibility of multidimensional remote monitoring of patient-reported outcomes and physiological parameters. Satisfactory compliance with the use of the app and smartwatch, whether confirmed or infirmed through this study, will be propaedeutic to the development of innovative mHealth interventions in survivors of cancer.

**International Registered Report Identifier (IRRID):**

PRR1-10.2196/52957

## Introduction

### Background

Cancer survivorship begins with the diagnosis and continues throughout the whole life span of the person [1]. Owing to repeated advances in anticancer and supportive treatments, survivors of cancer represent an ever-growing population [2]. Indeed, accelerated by the recent COVID-19 pandemic, alternative models of care for survivors of cancer are being proposed to meet the growing demands, driven by patient-specific issues and local health care resource constraints [3]. Survivors of cancer could be still receiving anticancer treatment, or they may have already completed treatment, albeit only temporarily. In the former case, acute toxicities from anticancer treatment might be the most relevant and bothersome, whereas in the latter case, delayed and long-lasting toxicities and a plethora of physical, emotional, social, practical, and informational issues become the most critical unmet care needs for their well-being [4].

Healthy lifestyle interventions have a positive impact on cancer-related outcomes, such as overall survival, tolerance to treatment, and health-related quality of life (HRQoL), as well as other metabolic and degenerative diseases [5]. Specifically, appropriate habitual physical activity, adequate sleep, and a regular wholesome diet are of paramount importance for the wellness of survivors of cancer [1] and are considered fundamental pillars of supportive care in survivors of cancer [6]. Thus, the promotion of interventions for healthier habitual nutritional, sleep, and physical activity behaviors is broadly recommended [7]. Nevertheless, there are motivational, practical, and informational barriers to the wide adoption of modifiable healthy lifestyle behaviors in survivors of cancer [8-10].

As a class of ubiquitous technologies, mobile health (mHealth) apps have the potential to support lifestyle interventions. The combination of wearables and smartphone sensors allows scalable and practically implementable study of human behavior and physiology [11]. Automatic collection of personal health data can be complemented by self-reported assessments delivered through mHealth apps, allowing real-time monitoring of patient-reported outcomes. Such a combination of mHealth data with electronic medical records and electronic health records also opens the possibility of a new breed of artificial intelligence (AI) apps, with the potential to facilitate early detection of new conditions, identify worsening of symptoms, and provide novel delivery methods for lifestyle interventions.

### Objectives

The European Union’s (EU’s) Horizon 2020 GATEKEEPER (GK) project is a flagship innovation action aimed at implementing this vision and delivering the future EU data and AI infrastructure for health care solutions [12]. GK has several goals, ranging from the technical software architecture and cross-countries’ and cross-organizations’ information security and data policy to the evaluation of data-driven services and AI-based interventions. GK’s key innovation is combining health medical records with medical sensors and non–medical data from mHealth apps, wearables, and smart devices. The intuition is that apps and devices would bring critical contextual and behavioral information that, combined with medical data and knowledge, would lead to a breakthrough in AI for health care. For instance, ongoing investigations within the GK project involve the development of risk prediction algorithms for mental health and cognitive impairment and digital coaching to mitigate loneliness-related risks [13]. These breakthroughs are the result of this new approach and the data sets collected as part of the project.

In this regard, GK includes a multicentric large-scale pilot across 8 EU and 3 Asian countries for a total of 11 Reference Pilot Sites. The large-scale pilot aims to develop and test a novel approach to the evaluation of digital innovation in health care. The proposed approach can be described as an integrative analysis of cost-benefits, combining the local evaluation of the wide range of approaches and solutions at the reference sites with 10 main health care themes [13]. Pilots within the GK project evaluate, monitor, or treat the most prevalent, chronic, noncommunicable conditions according to the World Health Organization, including cardiovascular, metabolic, and respiratory diseases, whereas this pilot study focuses on cancer [14].

Specifically, the proposed study is 1 of the 3 UK Reference Pilot Sites and falls under the Reference Use Cases on *co-morbidity and polymedication*. In preparation for the proposed study, a new mHealth solution for survivors of cancer was co-designed. This solution was initially tested in a small-scale study focused on the use of a wearable mHealth app before further expansion within the context of GK [13].

In the proposed study, behavioral data (nutritional intake, physical activity, and sleep) will be obtained through self-reporting (recorded via an app) and automatic collection (by a wearable smartwatch). The data will then be used for remote monitoring of cancer symptoms, automatic assessments of biometric data, and integration with health medical records. Thus, the aim of this study is to assess the feasibility of mHealth monitoring in survivors of cancer. It is hypothesized that mHealth monitoring will be feasible in survivors of cancer; specifically, at least 50% (50/100) of the participants will engage with the GK app at least once a week in 8 of the 16 study weeks.

## Methods

### Ethical Considerations

The study protocol has been approved by the National Health Services (NHS) Research Ethics Committee (Integrated Research Application System ID: 301068; Research Ethics Committee reference: 22//SC/0323) and therefore by the Health Research Authority and Health and Care Research Wales.

Informed consent describes both the primary and secondary uses of data. Concerning secondary uses, participants are informed about the full anonymization of their data with the aim of creating a resource for the study of predictors of symptom worsening, cancer relapse, and hospitalization events. The informed consent form is provided both in English and Welsh.

The study approval included a comprehensive data protection impact assessment and a data management plan concerning data flow, processing, and sharing. In summary, participants will be given a study code and an anonymous user account for the use of the wearable device and study app. The study will only use biometric data generated through commercially available systems—Samsung Health (SH) app and Samsung Galaxy Watch. The mHealth solution decouples and anonymizes data from their data vault on patients’ phones before transfer and processing. Only the hospital staff will have access to the identity or personal information of patients, and no other researchers involved will be able to access the registry of patient identifiers.

Participants will be gifted with the wearable device (smartwatch) and replacement Android phone (provided to iOS users). Furthermore, a form of compensation is the training in the use of these widely available technologies as well as the opportunity to learn more about how digital coaching and digital health technologies make use of personal data. Finally, the study will provide participants with the opportunity to reflect on the role of self-management and potential support available to them.

### Study Setting

This study is the result of a co-design approach involving the Betsi Cadwaldr University Health Board Cancer Services; specialists on nutrition, sleep, and physical activity; technology providers; AI researchers; experts on clinical research and evaluation; acute medicine physicians; and patients with cancer. Over a period of 2 years, weekly meetings between main investigators and technical partners, focus groups with patients with cancer, and a cocreation group involving all stakeholders generated a patient-facing app, a clinician facing dashboard, AI algorithms, communication and training materials, and specialist outcome assessments, which led to an mHealth solution that could be pragmatically implemented alongside current routine care for survivors of cancer, as provided by the public health care system, NHS Wales.

The study design is also the result of learning from other GK Reference Pilot Sites. In this regard, we propose a feasibility design with a duration of 16 weeks, which will be conducted at a single institution, the Oncology Service of Ysbyty Gwynedd Hospital, Bangor, Wales, United Kingdom.

### Eligibility Criteria

To be enrolled in the study, all participants must meet all the following requirements: (1) diagnosis of any solid malignancy, at any stage; (2) completion of treatment (including surgery, radiotherapy, and any type of systemic anticancer treatment); (3) clinical, biochemical, and radiological confirmation of controlled disease (no evidence of residual disease or nonprogressive disease); (4) scheduled for either a therapeutic break (from systemic anticancer treatment) or having completed the planned multimodal treatment; (5) scheduled for active surveillance plan within the oncology service; (6) male or female patients aged at least 18 years; and (7) scored World Health Organization performance status 0 to 2 [15].

Patients will be excluded from participating in the study if they meet any of the following criteria: (1) not possessing a SIM card, (2) no internet access through Wi-Fi or unwilling to use mobile data allowance on a daily basis, (3) inability to understand and follow the instructions autonomously, (4) uncontrolled severe comorbidities (eg, cardiovascular, metabolic, neurological, and respiratory), (5) lack of capacity, (6) inability to understand English, (7) still undergoing systemic anticancer treatment (apart from bone-targeted agents, hormonal treatment against breast or prostate cancers, or maintenance monoclonal antibody monotherapy), (8) poor general condition (performance status>2), and (9) inability to sign informed consent.

We decided to focus on survivors of cancer who were not receiving anticancer treatment to minimize the potential impact of treatment-induced fatigue or anorexia. On the basis of previous discussion with patients with cancer, it was felt that this population was the most suitable to test our mHealth solution in the first place, which can be adapted in future studies to the needs of patients on active disease-modifying treatment.

### Digital Health Care Technology

#### SH App and Samsung Galaxy Watch

The SH app, coupled with Samsung Galaxy Watch, can track a number of parameters, including (1) food and water intake (including calorie tracking), (2) sleep patterns, (3) blood oxygen saturation levels, (4) body composition, (5) body weight, (6) calorie intake, (7) heart rate, (8) blood pressure, and (9) habitual physical activity (step counts and minutes of moderate and physical activity completed per day).

The SH app uses biometrics obtained by the connected wearable device, the smartphone itself, and self-reporting to record variables such as accelerometry, heart rate, time, distance traveled, and speed. Data are then used for activity tracking by matching the signature characteristics of a wide range of exercises (such as walking, hiking, or swimming) to calculate step counts, the number of minutes of moderate and vigorous physical activity completed, and the number of calories expended. The SH app supports tracking of food intake during the day. For instance, users can record meals and snacks as well as fluid and caffeine intake. Macronutrients (proteins, carbohydrates, and fats) and micronutrients (vitamins and minerals) can be calculated. The SH app also implements sleep analysis, sleep duration tracking, and sleep stages to provide insights about the quantity and quality of sleep.

#### GK App

The GK app is an mHealth solution that will be installed on a personal smartphone and paired with the SH app. Patients will use it to periodically fill self-assessment questionnaires and view data visualization analytics.

#### Web Portals and Tablets

To complement the data collected by the SH app, Samsung Galaxy watch, and GK app, the patients will fill in questionnaires. These questionnaires will be completed by patients using a tablet, and paper forms will be provided in cases where a tablet is not available. The questionnaires will cover data describing HRQoL, symptoms, sleep, and patient feedback on care. Patients will also use an web-based survey platform (Qualtrics) to fill in questionnaires about habitual physical activity, any structured exercise completed, and patient activation.

### Recruitment Program

Participants will be identified from oncology services at Ysbyty Gwynedd Hospital, Betsi Cadwaladr University Health Board, by reviewing the outpatient clinic lists of each participating oncologist, advanced nurse practitioner, and clinical pharmacist on a daily basis. For potentially eligible patients, the appropriateness of proposing participation in this trial will be decided by the lead oncologist. At the end of the clinical consultation, if deemed appropriate, the clinician will introduce the study and provide the information leaflet, and a date in the future will be set for the volunteer to meet a member of the clinical research team to answer all the possible queries and to confirm sign-up for participation. If and when a participant agrees to proceed with the study, they will be asked to sign the consent form and will receive the smartwatch (and a smartphone, if required). The clinical research team member will help with the setup of the apps and smartwatch pairing and will provide a technical overview of both as well as the troubleshooting and contact information. Baseline questionnaires will be completed on a dedicated tablet or paper as per the recommended procedures with a standard approach to collect these patient-generated data with the supervision of the clinical research nurse or officer [16]. The same approach will be used to collect end-of-study questionnaires data. The expected recruitment period is January 2024 to June 2024, with the maximum duration of data collection for each participant set to up to 16 weeks. We anticipate being able to recruit about 5 patients per week over a 24-week period to reach our target.

### Contingency Plans for Potential Recruitment Risks

For this monocentric pilot, we have built on previous experience within the oncology department with digital monitoring studies [17-19], and the estimated recruitment has been discussed at length between clinicians and research team members. A risk assessment analysis has been performed, and no transfer, avoidance, or prevention of the risk of poor recruitment has been identified. To mitigate the risk of lower than expected acceptance from the patients, we have trained the involved clinician to present the study to their patients, who were potentially eligible for participation, rather than simply referring them to the research team for study explanation. To mitigate the risk of poor engagement from the clinicians themselves, we have already involved them since the beginning of the study, and we have planned meetings between the delivery research team and clinicians after multidisciplinary team meetings to remind them of the study objectives and inclusion criteria. We have also printed a leaflet containing the main study features for each relevant outpatient clinic. Finally, we decided to accept the risk of slow recruitment as, within the GK project, we have no further studies pending upon the results of this study.

### Study Procedures

Following the provision of written informed consent, the following measures will be obtained and recorded in the case report form (CRFs) at baseline and at the end of the study (16 weeks):

Height (only measured at study entry)Body massBMIWaist circumferenceHip circumferenceMedical historyConcurrent conditionsConcomitant medicationsWHO performance status [15]Cancer type and stageHarms—adverse events.

We will record and report “unexpected” serious adverse events resulting in death, life-threatening complications, hospitalization or prolongation of existing hospitalization, persistent or significant disability or incapacity, congenital abnormality or birth defect, and other “important medical events” that are considered serious if they jeopardize the participant or require an intervention to prevent 1 of the abovementioned consequences.

The following adverse events are considered to be “expected”: anxiety related to the monitoring of symptoms, diet, and exercise; distress related to the regular use of digital well-being technology; cutaneous allergic reactions to the smartwatch; and visual strain with the light-emitting smartphone screen.

The study uses the following questionnaires:

EQ-5D-5L: Participants’ HRQoL will be measured using the EQ-5D-5L questionnaire [20]. EQ-5D-5L is a widely used tool for assessing the domains of mobility, self-care, usual activities, pain or discomfort, and anxiety or depression as well as recording patients’ self-rated health on a visual analog scale.Multidimensional Fatigue Inventory Short Form: Multidimensional Fatigue Inventory Short Form [21] will be used to assess fatigue. This is a validated short form of the more in-depth Multidimensional Fatigue Inventory questionnaire [22] and uses 10 simple questions to assess physical, emotional, and cognitive fatigue [21].Satisfaction, Alertness, Timing, Efficiency and Duration (SATED): The SATED questionnaire [23] will be used to assess subjective sleep. SATED is a simple questionnaire to determine the degree of sleep fulfillment and to measure the dimensions of sleep health based on 5 simple questions [24]. It has been used in >150 peer-reviewed papers and studies.Patient Assessment of Chronic Illness Care: Patient Assessment of Chronic Illness Care questionnaire [25] will be used to assess experience with care. It is recommended for research and quality improvement and has been successfully deployed in digital oncology studies [26].Edmonton Symptom Assessment System (ESAS; digital form completed daily through the GK app): The global symptom burden will be assessed through ESAS [27]. ESAS has a recall time of 24 hours and is adapted to daily completion [28]. Daily total symptom distress scores (ESAS physical score+emotional score+well-being) [29] will be computed, and their temporal trajectories will be compared using general linear and random mixed effects models for longitudinal data [30].Global Physical Activity Questionnaire: Habitual physical activity will be assessed using the Global Physical Activity Questionnaire short form [31] and four unvalidated questions: (1) minutes of moderate physical activity completed per week, (2) minutes of vigorous physical activity completed per week, (3) number of sessions of strength training completed per week, and (4) number of sessions of balance training completed per week.Patient Activation Measure–13: Patient activation, an individual’s knowledge, skills, and confidence integral to managing their own health and health care, will be assessed using the Patient Activation Measure–13 [32].

Table 1 lists the timeline and type of data collected throughout the study period.

Participants will then be presented with the mHealth solution: the GK app on a personal smartphone and a smartwatch paired with the SH app. The participant will be trained to use the apps and watch. The GK app features a set of interactive questionnaires to collect the baseline and periodic self-assessment data. Furthermore, the GK app provides timely reminders about the need to complete the self-assessments and data visualization analytics. Finally, the GK app collects and anonymizes data from the smartwatch and SH app for daily data collection on a dedicated remote server. The smartwatch adopted can be configured and used in different ways; each patient will be able to set up complementary apps offering extra functionalities such as the stress level analysis and to identify the preferred patterns of use. Overall, the data generated by the smartwatch will be collected and aggregated on a daily basis, including heart rate, sleep and physical activity patterns, and calories and food intake. The sampling of data will be dependent on the user settings and contingencies, such as charging at night or battery level. Throughout the 16-week study period, the smartwatch will continuously and unobtrusively record habitual physical activity, sleep patterns, energy expenditure, step counts, and oxygen saturation through its biosensors (Figure 1). For example, the amount of moderate and vigorous physical activity completed per week will be obtained automatically through the study using heart rate data recorded by the wearable smartwatch. Specifically, the maximal heart rate will first be predicted using the following formula: maximal heart rate = 207 − (0.7 × age) [33].

**Table 1 table1:** Data collected at each time point of the study.

	Baseline: day 0	Day 1-14	Daily from baseline	Thrice weekly (alternate days)	Weekly	End of the study (4 months +7 or −7 days)
Eligibility	✓					
Informed consent	✓					
Demographics	✓					
Height, weight, BMI, and waist circumference	✓^a^					✓
WHO^b^ performance status	✓					
Medical history or concomitant conditions and medications	✓					✓
Cancer type and stage	✓					
ED-5D-5L	✓^a^					✓
MFI^c^-10	✓^a^					✓
SATED^d^	✓^a^					✓
PACIC^e^	✓^a^					✓
PAM 13^f^	✓^a^					
Issue of smartwatch and Android device if required	✓^a^					
Food diary				✓		
Weight					✓	
Physical activity appointment including cardio-respiratory fitness and muscular strength		✓				
GPAQ^g^		✓				✓
Habitual physical activity assessment		✓				
Minutes of activity done by patient including strength and balance					✓	
Borg’s CR100 rating of perceived exertion scale					✓	
ESAS^h^			✓			✓
Continuous smartwatch data collection	✓^i^	✓	✓			
Usability questionnaire						✓
Adverse event assessment	✓^i^	✓	✓	✓	✓	✓
Collection of UKONS^j^	✓^i^	✓	✓	✓	✓	✓

^a^Conducted in person at baseline assessment visit.

^b^WHO: World Health Organization.

^c^MFI-10: Multidimensional Fatigue Inventory Short Form.

^d^SATED: Satisfaction, Alertness, Timing, Efficiency and Duration.

^e^PACIC: Patient Assessment of Chronic Illness Care.

^f^PAM-13: Patient Activation Measure–13.

^g^GPAQ: Global Physical Activity Questionnaire.

^h^ESAS: Edmonton Symptom Assessment System.

^i^To be collected from informed consent onward.

^j^UKONS: United Kingdom Oncology Nursing Society.

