**Figure 1 figure1:**
[figure not shown]
Study schematic of the trial design (longitudinal and observational) with features of the patient-generated data collected through the smartwatch (objective and mostly continuous) and app (subjective and repeated measures or snapshots).

If a patient obtains a higher than predicted maximal heart rate during exercise, the actual maximal heart rate will replace the predicted maximal heart rate. The resting heart rate will then be recorded automatically by the watch. Heart rate zones will then be used to identify habitual physical activity intensity: very light (<30% heart rate reserve [HRR]), light (30%-39% HRR), moderate (40%-59% HRR), vigorous (60%-89% HRR), and near maximal to maximal (≥90% HRR) [34].

Energy expenditure during structured exercise will be estimated from the power output calculated from the mode of exercise, distance completed, and floors climbed. Other measurements such as body fat percentage, oxygen saturation, and blood pressure will be obtained using the standard features available within the smartwatch and smartphone.

The smartwatch will also prompt the participant to complete the ESAS questionnaire on a daily basis and to self-report the amount of habitual physical activity using the 4 abovementioned unvalidated questions on a weekly basis.

The SH app uses the Samsung Galaxy Watch to monitor sleep patterns, track sleep movements, and generate a sleep score. Additionally, the SH app provides daily goals and coaching programs based on sleep data to help improve sleep habits. Sleep analysis uses Samsung proprietary algorithms currently available through the public release of the SH app.

The SH app also allows the self-logging of the type and timing of meals and snacks. It is possible to set a daily target for caloric intake. After inputting details of the food type and quantity from a menu of common meals, the SH app provides a real-time view of the current calorie count for the day and a summary of the nutritional intake to determine if one is within the recommended levels. Moreover, it provides access to an overall dietary report over the span of a week.

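### Heart-rate-based activity minutes use an age-predicted maximum that can only be revised upward, so they are understated for participants on permitted rate-lowering drugs; a medication-flagged sensitivity analysis would show by how much

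*Protocol article*

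**What the plan says.** Study Procedures in the protocol article states that "the amount of moderate and vigorous physical activity completed per week will be obtained automatically through the study using heart rate data" from the watch. To that end, "the maximal heart rate will first be predicted using the following formula": 207 − 0.7 × age. The text after Figure 1 adds one correction: "If a patient obtains a higher than predicted maximal heart rate during exercise", then "the actual maximal heart rate will replace the predicted maximal heart rate". No counterpart is given for a maximum below the prediction. The lower end of the scale is individual: "The resting heart rate will then be recorded automatically by the watch". Intensity is then graded by percentage of heart rate reserve (HRR): very light below 30, light 30–39, moderate 40–59, vigorous 60–89, near maximal 90 and above.

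On who may enter, exclusion criterion 4 (Eligibility Criteria) is limited to "uncontrolled severe comorbidities (eg, cardiovascular, metabolic, neurological, and respiratory". Exclusion 7 concerns systemic anticancer treatment only. The section on concomitant care allows, and records, any intervention for an intercurrent problem. Table 1 schedules "Medical history or concomitant conditions and medications" at baseline and end of study. No passage links that record to the heart rate zones, and the preplanned subgroups in Statistical Considerations (data completeness, performance status, evidence of disease, sex, age) do not include medication.

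**The concern.** A participant with controlled, treated cardiovascular disease can enrol, and may be taking a drug that limits heart rate. The watch's resting rate will reflect that drug; the age formula cannot. The predicted maximum is then too high, the reserve too wide, and every cut-off too high. Because the only permitted correction is upward, data from such a participant can never bring the maximum down.

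The error runs in one direction and falls on a group that can be identified from data already collected. Secondary Outcomes says that these measures serve to explore the direction and effect size of changes, as groundwork for later trials. An understated activity level, or an apparent change produced by a change of medication, would carry into that groundwork.

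**Working it through.** The plan states no figure of its own for this point, so the check applies its formula and zones.

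**Inputs from the protocol article**
- Predicted maximum: P = 207 − 0.7 × age.
- Cut-off for a fraction f of reserve: R + f × (P − R), where R is the resting rate. Moderate starts at f = 0.40, vigorous at f = 0.60.

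**Inputs assumed (not in the documents)**
- Age 65, resting rate on drug 60 beats/min.
- True maximum d = 10, 20 or 30 beats/min below P.
- That some drugs lower the achievable maximum is taken as general pharmacology.

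**Cut-offs as written**
- P = 207 − 0.7 × 65 = 161.5; reserve = 161.5 − 60 = 101.5.
- Moderate: 60 + 0.4 × 101.5 = 100.6. Vigorous: 60 + 0.6 × 101.5 = 120.9.

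**Cut-offs with the true maximum P − d**

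The true reserve is 101.5 − d, so the moderate cut-off is overstated by 0.4d and the vigorous cut-off by 0.6d.

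| d | True reserve | True moderate cut-off | Excess (0.4d) | True vigorous cut-off | Excess (0.6d) |
|---|---|---|---|---|---|
| 10 | 91.5 | 96.6 | 4 | 114.9 | 6 |
| 20 | 81.5 | 92.6 | 8 | 108.9 | 12 |
| 30 | 71.5 | 88.6 | 12 | 102.9 | 18 |

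**Share of the true moderate band (40–60% of reserve) scored below moderate**

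The written moderate cut-off lies 40.6 beats above rest.
- d = 10: 40.6/91.5 = 44.4% of true reserve; (44.4 − 40)/20 ≈ 22%.
- d = 20: 40.6/81.5 = 49.8%; (49.8 − 40)/20 ≈ 49%.
- d = 30: 40.6/71.5 = 56.8%; (56.8 − 40)/20 ≈ 84%.

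For ages 50–75 and resting rates 55–70, the same calculation gives about 19–27%, 41–62% and 69–100%.

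**Where the displaced activity goes**
- At d = 30, an assigned 30% corresponds to a true 30 × 101.5/71.5 = 42.6%. About (42.6 − 40)/20 = 13% of the moderate band therefore scores as very light, and the rest of the displaced part as light.
- The written vigorous cut-off lies 60.9 beats above rest: 60.9/91.5, 60.9/81.5 and 60.9/71.5 give a true 66.6%, 74.7% and 85.2%. True vigorous activity below those points scores as moderate and partly refills that category.
- Time at or above the moderate cut-off, all higher zones combined, can only fall.

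**Drug started during the study (illustration)**

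Let the resting rate go from 70 to 60 and the maximum from 161.5 to 141.5, with exercise at a constant true 45% of reserve.
- Before: rate 70 + 0.45 × 91.5 = 111.2; cut-off 70 + 0.4 × 91.5 = 106.6; scored moderate.
- After, resting rate updated: rate 60 + 0.45 × 81.5 = 96.7; cut-off 100.6; scored light.
- After, resting rate not updated: cut-off stays at 106.6, and 96.7 is again below it.

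Relative effort is unchanged, yet the recorded category falls either way.

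**The case against.** The best defence of the rule is logical. A higher observed rate disproves the prediction, whereas a free-living peak below it may only mean that the participant did not exert fully. Upward-only revision is therefore sensible for watch data, and that stands: the rule is not wrong in itself. It does not help a participant whose maximum is lowered by a drug.

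The measured resting rate compensates only in part. It sets the lower end of the reserve, and the excess of 0.4d is calculated with that rate already on drug.

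Parallel measures exist: the Global Physical Activity Questionnaire, weekly self-reported minutes, Borg CR100 and step counts. Table 1 also lists a fitness appointment on days 1–14, but the zone rule does not say it is used. These measures soften the consequence without correcting the heart-rate-based minutes.

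It can also be said that medication flags belong in an analysis plan that is not shown. That is fair for the flag. The scoring rule, however, is stated in full in the article and errs one way when followed.

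Several stronger readings are tempting and not supported:
- That this is a key outcome. Secondary Outcomes ranks nothing, and Study Procedures introduces these minutes as an example.
- That moderate minutes alone must fall. Vigorous activity scored as moderate can refill them.
- That 22%, 49% or 84% of minutes are lost. These are shares of an intensity band; the loss in minutes depends on how time is spread across it.
- That the circadian parameters share the fault. Their methods are not said to use a predicted maximum.

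**Conclusion.** The point holds as a modest improvement. The documents establish the age-predicted maximum, the upward-only revision and the absence of any exclusion of rate-lowering drugs. For anyone whose true maximum lies below the prediction, combined moderate-plus-vigorous minutes are understated, and the excess in the cut-offs (0.4d and 0.6d) follows from the plan's own formula.

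The size rests on assumptions. The documents name no such drug and give neither its effect on the maximum nor the number of users. At an assumed 10 beats/min only about the lowest fifth of the moderate band moves; at 30, most of it does. If 10% to 30% of 100 participants were users, 10 to 30 people would be affected.

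With stable medication the bias falls mainly on absolute levels; a drug started or stopped between baseline and end can mimic a change. The measure is one exploratory secondary outcome in a single-arm pilot, and no traffic-light criterion uses heart rate zones.

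**What to change.** Keep all participants in the main summary, in line with the intention-to-treat basis that Statistical Considerations sets for secondary outcomes. Then:

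1. Derive one flag from the concomitant medication recorded at baseline and end of study: on a rate-lowering drug at either time, and started or stopped between them.
2. Prespecify a sensitivity analysis of heart-rate-based minutes, and of their change, that excludes flagged participants, including those who started or stopped such a drug.
3. For flagged participants, interpret activity from step counts or accelerometry. The Samsung Health activity minutes are not a clean substitute, because the section describing that app lists heart rate among its inputs.

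The flag need not extend to the circadian analyses. Making unflagged participants the main result would reverse the plan's stated order and remove people with treated cardiovascular disease from the headline figure, so the restricted set should remain a sensitivity analysis.

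The cost is one derived variable and one small added analysis, with no new data and no change to care. The downside is that the sensitivity set is smaller and selected, and should be reported as such.
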